## 3. Data Collection, Management, and Statistical Analyses

### 3.1. Clinical Data

The clinical part will be mainly recorded in the case report form and the clinical laboratory results. After the study is completed, the principal investigator will sign off on each case report form and the data lock date will be confirmed. After the data lock is set, the data will be transcribed into a data management Excel sheet to monitor the data entry activity. The data management sheets will include the demographic data, vital signs, clinical laboratory data, actual sampling time points, dosing time points, and adverse events.

The forms and templates that will be used throughout the data collection, management, and statistical analyses are outlined in Figure 4. The subject demographic data and laboratory characteristics for screening and post-dose monitoring will be tabulated. The number of adverse drug reactions will also be recorded accordingly. A list of tables, listings, and figures will be generated for the study report (Supplementary Figure S7).

### 3.2. Pharmacokinetics Analysis

This study will involve the collection of biological samples in triplicate. The first set of samples will be used for the pharmacokinetics analysis. The blood samples for each time point will be analysed using liquid chromatography mass spectrometry (LCMS) to determine the subject’s plasma concentration of the active ingredients: metformin, andrographolide, neoandrographolide, and deoxyandrographolide. Additional plasma samples will be collected for the purpose of method validation according to the guidelines for bioanalytical method validation [46]. The method validation parameters will include the accuracy, precision, calibration curve, and quality control samples during the study validation. The internal standard will be spiked into each sample to ensure consistency among all of the peaks.

The individual subject plasma concentration will be used for the pharmacokinetics profile calculation to produce the drug concentration time–curve. Non compartmental analysis will be performed using MATLAB SimBiology software. The pharmacokinetics profile of Cmax, AUC, Tmax, and volume of distribution (Vd) will be determined for metformin 1000 mg, AP 1000 mg, and 2000 mg.

### 3.3. Untargeted Metabolomics and Multivariate Data Analysis

In the metformin analyses, pharmacometabolomics analysis will be performed to explore the human metabolic pathways between the pre-dose and peak plasma concentration. The samples will be analysed using Agilent LCMS-QTOF for an untargeted metabolomics approach following the literature method with some modification [47]. The samples will be analysed using a reverse phase column with a guard column in both the positive and negative modes. The instrument method setting will follow the METLIN analysis methods [48]. The pool quality control samples will be used to condition the column and visualisation checking for the batch analysis.

The untargeted metabolomics workflow is presented in Supplementary Figure S8. The chromatograms will be converted to the mzXML file using Global Natural Products Social (GNPS) package, University of California San Diego, California, United States [49]. MS spectral processing, normalisation, batch correction, multivariate analysis, and functional metabolic pathway analysis will be run on MetaboAnalyst web-based application (McGill University, Montreal, QC, Canada) to identify the human metabolic pathways [50]. In the multivariate analyses, principal component analysis (PCA) and partial least square discriminant analysis (PLSDA) will be used to inspect the region’s separation among the analysed time points. After this, a t-test will be used to identify the significantly differentiated compounds between the two-time point groups. The significant features will be processed in MS peaks to a pathway module to identify the dysregulated human metabolic pathways according to the Kyoto Encyclopaedia of Genes and Genomes (KEGG) database.

A similar analysis framework for metformin as described above will be repeated for AP 1000 mg and AP 2000 mg. There will be a head-to-head comparison of the pharmacokinetic profiles for both the AP arms. After this, the pharmacometabolomic identified dysregulated human metabolic pathways will be compared for the two doses in AP to investigate the dose-dependent effects. Finally, the dysregulated human metabolic pathways associated with the diabetic effects for the metformin, AP 1000 mg, and AP 2000 mg will be compared.

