#### 2.3.4. Assignment of Intervention, Randomisation, and Blinding

The three-period, six-sequence, permuted block randomisation sequence will be generated using statistical software SAS Enterprise Guide version 7.1, SAS Institute Inc., Cary, NC, USA. The seed code 736522 was generated for the purpose of reproducibility, and the source code is attached in Supplementary Figure S2. The randomisation code will be given to the pharmacist to perform the investigated product dispensing for three formulations: code A for metformin 1000 mg, code B for AP capsules 1000 mg, and code C for AP capsules 2000 mg.

Both the metformin tablets and AP capsules are registered with the Ministry of Health Malaysia. The investigational product accountability was recorded by the pharmacist. Dispensing activities were performed according to the line clearance procedures to avoid cross contamination or dispensing errors (Supplementary Figure S3). Another pharmacist will monitor each dispensing activity and a duplicate sticker labelled with the investigational product name (Supplementary Figure S4), protocol number, and other details will be attached to the envelope.

This will be an open-label pharmacokinetics and metabolomics study. Prior knowledge of the investigational product administration to the subject does not affect the bioavailability and metabolic effects of the drug. The blinding procedure will not be applied in this study so the investigator and the subjects are aware of the type of investigational products being administered during the clinical trials.

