#### 2.3.6. Sample Size Calculation

This is a proof-of-concept pharmacokinetics and pharmacometabolomics exploration study to determine the pharmacokinetic parameters and human metabolic pathways. The objective of a pharmacokinetics study in a phase I trial is to mainly measure the characteristic of the drug, so there is no statistical basis to determine the sample size. The number of subjects usually ranges from 4 to 24 subjects [38]. The United States guidance recommended a minimum of 12 subjects at each arm in the pharmacokinetics bioequivalence study [39]. Another sample size estimation approach for metabolomic analysis without the experimental pilot data proposed 12 subjects in each group using dynamic probabilistic principal component analysis or 18 subjects in each group for the probabilistic principal components and covariates analysis [40]. This study will recruit 18 subjects in each formulation considering the phase one features and analyses to plan for the pharmacokinetics and metabolomics.

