#### 2.3.7. Screening and Data Collection

Subjects will be screened for the eligibility criteria according to the screening case report form after signing the informed consent form. The principal investigator will perform the physical examination, review the demographic data, electrocardiogram, vital signs, biochemistry, haematological, serological, urinalysis test, and perform the interview questionnaire to determine the subject’s eligibility. Eligible subjects will attend the dosing day at the trial site and will be asked to fast for at least ten hours to reduce the variability of drug absorption. Eligible subjects will then be asked to attend a method validation visit to collect additional blood and urine samples.

On the dosing day, the study coordinator will record the subject attendance list, subject enrolment list, subject identification list, and subject randomisation sheet. Subjects will be assigned to the randomisation group by the study coordinator. Pre-dose urine samples and plasma samples will be collected before dosing. After single-dose oral administration, fourteen blood samples will be collected at 0.5, 1, 1.5, 2, 2.5, 3, 3.5, 4, 5, 6, 8, 10, 12, and 24 h post-dose. The actual sampling time will refer to the subject plasma sampling schedule (Supplementary Figure S6) and subject urine sampling schedule. An indwelling intravenous cannula will be used to collect the pre-dose and up to 12 h post-dose blood sample by syringe. The blood samples will then transferred into a pre-labelled potassium ethylenediaminetetraacetic acid (KEDTA) tube. The heparin-lock technique will be performed to prevent clotting of the blood by injecting 1 mL of heparinised saline in the indwelling cannula. Ambulatory blood will be collected at 24 h post-dose. The blood samples will then be centrifuged at 35,000 rpm for 15 min at 20 °C, and the plasma separated into three aliquots in cryotubes and stored at −80 °C in a freezer. The post-dose urine samples will be collected at three periods: period U1 (0–4 h post-dose), U2 (4–8 h post-dose), and U3 (8–12 h post-dose. The urine samples will then be separated into three aliquots in cryotubes and stored at −80 °C in a freezer. The study activities will be recorded on the case report form.

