## 4. Discussion

This proof-of-concept study protocol aims to determine the pharmacokinetics and explore the metabolomics profiling of metformin and AP capsules for application in early-phase clinical trial. The protocol describes the conduct of clinical trials with comprehensive methods and Supplementary Documents that comply with the principle of Good Clinical Practice and relevant trial-related forms to record the clinical outcomes.

The pharmacokinetics and bioavailability study could determine the rate and extent of the drug being absorbed into the human blood circulation [27]. From the first metformin analysis dataset, the individualised peak plasma concentration obtained from the pharmacokinetics study will be used to explore the human metabolic pathways. This approach can identify the dysregulated human metabolic pathways associated with the pharmacological effect accurately based on the peak plasma concentration of the drug. Therefore, the combination of a pharmacokinetics and pharmacometabolomics study could complement the interpretation of the human metabolic pathways during peak plasma concentration.

In the second phase analyses, the two doses of AP capsules arms provide additional information about the pharmacokinetics profiles characteristic of the three biomarkers, andrographolide, neoandrographolide, and deoxyandrographolide. The pharmacometabolomic analysis for the two doses of AP capsules potential identify dose-dependent metabolic signatures with intense metabolic features at affected human metabolic pathways associated with the pharmacodynamic effects.

This study will employ a crossover design instead of the typical 6 + 2 dose escalation first-in-human study design to reduce the variability of the trial subjects in metabolomic study, shorten the trial duration, and maximise the resources to recruit different subjects. The study protocol is practical for institutional academic research compared to complex industry sponsor regulatory trials while complying with the Good Clinical Practice principle. This study potential provides a framework for the application of a pharmacokinetics and metabolomics approach in a phase one trial, which could reveal valuable drug intervention dysregulated human metabolic pathways or molecular drug effects through metabolomics analyses.

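### Metabolic pathways are attributed to a drug from uncontrolled pre-dose versus peak tests within each treatment, and the cross-treatment step compares pathways rather than within-subject changes

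*Protocol article*

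**What the plan says.** Section 3.3 fixes the contrast and the test. For metformin, "pharmacometabolomics analysis will be performed to explore the human metabolic pathways between the pre-dose and peak plasma concentration", and then "a t-test will be used to identify the significantly differentiated compounds between the two-time point groups". Significant features go to a pathway module, and the pathways that come out are called dysregulated. For the herbal arms, "A similar analysis framework for metformin as described above will be repeated for AP 1000 mg and AP 2000 mg". The pathways found are then compared between the two AP doses and, last, across all three treatments (also in the Objectives and section 3.4).

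The Abstract links these pathways to pharmacodynamic effects. The Discussion goes further: "This approach can identify the dysregulated human metabolic pathways associated with the pharmacological effect accurately", on the ground that sampling is at the drug's peak concentration.

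The randomised treatments are "code A for metformin 1000 mg, code B for AP capsules 1000 mg, and code C for AP capsules 2000 mg" (section 2.3.4). No period is without drug. On size, "This study will recruit 18 subjects in each formulation" (section 2.3.6).

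**The concern.** A test of pre-dose against peak within one treatment measures everything that changes between the two draws. The drug is one such thing. The length of the fast and the time of day are others, and they change in every subject in every period. The trial looks for pathways tied to glucose lowering, for which a longer fast is an obvious rival explanation. The document gives no figure for how large that rival effect might be.

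The later comparison across treatments does not remove the problem, because its inputs are the results of the separate pre/post tests. Two errors can follow:

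- A drift present in all periods can enter all three results and be read as a mechanism common to metformin and AP.
- A feature that is significant at one AP dose and not at the other can be read as dose dependence, although the difference between the doses has not been tested.

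**Working it through.** **No planned figure to reproduce.** Section 2.3.6 gives 18 subjects without an effect size, SD, significance level or power. The point does not depend on how 18 was reached.

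**Step 1: what changes between the draws.** Inputs: a fast of at least 10 h before dosing (section 2.3.7); lunch at 12.20 pm (section 2.3.7), given 4 h post-dose (section 2.4); Tmax 1.63 to 2 h for AP and 2 h for metformin (section 2.1), with 2.5 h for metformin in the Introduction.

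Dosing time is about 12:20 − 4 h = 08:20.

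| Tmax | Clock time at peak | Fast at peak (10 h + Tmax) |
|---|---|---|
| 1.63 h | about 09:57 | at least 11.6 h |
| 2 h | about 10:20 | at least 12 h |
| 2.5 h | about 10:50 | at least 12.5 h |

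A peak sample at these times comes before lunch, so the subject is still fasting.

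**Step 2: how often a drug-free drift is flagged.** Assumptions, none of them in the document: two-sided 5% per feature, no multiplicity adjustment, zero drug effect, and a drift of d SD. Section 3.3 does not say whether the t-test is paired, so both forms are shown.

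- Paired: noncentrality d√n with 17 df. For n = 18 this is 0.5 × 4.243 = 2.12 and 1.0 × 4.243 = 4.24. The unit is the SD of the change.
- Unpaired, treated as independent samples: noncentrality d√(n/2) with 34 df. This is 0.5 × 3 = 1.5 and 1.0 × 3 = 3.0. The unit is the SD of a single measurement.

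| Assumed drift | Paired | Unpaired |
|---|---|---|
| 0 | 5% | 5% |
| 0.25 SD | 17% | 11% |
| 0.5 SD | 52% | 31% |
| 0.75 SD | 85% | 59% |
| 1.0 SD | 98% | 83% |

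**Step 3: all three treatments together.** In 20,000 simulated trials, each with 18 subjects, three periods, the same drift in each period, independent changes with SD 1 and a paired test, all three treatments were significant in 14% of runs at 0.5 SD and 94% at 1.0 SD. The product of the single rates agrees: 0.516³ = 0.137 and 0.979³ = 0.938.

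**Step 4: apparent dose dependence.** Under the same assumptions, the chance that exactly one of the two AP doses is significant is 2 × 0.516 × 0.484 = 0.50 at 0.5 SD and 2 × 0.979 × 0.021 = 0.04 at 1.0 SD. A moderate drift with no drug effect at either dose would therefore look dose-specific about half the time.

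**Step 5: the within-subject contrast.** In the same simulation, testing the difference in change between two treatments within subjects flagged 5.2% at 0.5 SD and 4.8% at 1.0 SD, close to the nominal 5%. This holds if the drift is equal across the treatments compared, which requires samples at like times.

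**The case against.** The study is exploratory and says so. The article rests on a full protocol and a workflow figure in its supplements, which are not shown. A crossover model may be set out there or in an analysis plan, so its absence from the article is not itself a fault. That is accepted. What remains is what the article does fix: the selecting contrast, and the attribution drawn from it.

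The accuracy claim in the Discussion can be read as praise for sampling at the peak, not as a claim to have separated drug from fasting. That reading is fair, but timing the sample to the peak does not supply a control.

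The remedy is also partial. With no undosed period, the treatment contrast cannot give any one drug's absolute effect, and an effect that metformin and AP truly share cancels. The Abstract uses individual Cmax for metformin and median Cmax for AP, so elapsed time may differ by treatment and drift may not cancel fully.

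A reader might infer more than the document supports:

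- *That every change is credited to the drug.* Only significant features that map to pathways are interpreted.
- *That the crossover comparison goes unused.* Treatments are compared, at pathway level.
- *That heparin is an established cause.* Section 2.3.7 describes "injecting 1 mL of heparinised saline in the indwelling cannula", but pre-dose and later draws up to 12 h use the same cannula, and the first flush is not timed against the pre-dose draw. A difference in exposure is possible, not documented.
- *That posture differs.* Only the posture after dosing is stated.

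**Conclusion.** The point holds in limited form. Attribution of pathways to a drug rests on separate pre/post tests without a control, and comparing the resulting pathways does not remove a drift common to all periods. The confounding with time of day and with about 1.6 to 2.5 h of further fasting follows from the document's own meal times and Tmax values.

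The percentages are illustrations. Drift size, pairing, the 5% level, independence of the changes and equal drift across periods are all assumed, and a multiplicity correction would lower the rates. They show that a moderate drift would often be flagged, not that such a drift exists. Nor do they show that any pathway reported for metformin is wrong. For an exploratory study this is an inexpensive improvement to interpretation, not a defect that invalidates the trial.

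**What to change.** 1. Keep the pre-dose versus peak test within each treatment, labelled as descriptive.
2. For each feature, model log(post-dose/pre-dose) with treatment, period and sequence as fixed effects and subject as random. Use post-dose samples at a common nominal time where available; otherwise check sensitivity to time since dose. Such a covariate may be partly collinear with treatment, given the individual and median Cmax rules.
3. Base claims of treatment-specific or dose-dependent effects on the treatment contrasts from this model.
4. Label features that shift alike in all three arms as not separable from time and fasting.
5. Soften the accuracy claim in the Discussion, for example to pathways that change between pre-dose and peak concentration.

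**Cost.** Analysis code and wording, using the crossover data, with no new subjects. If the peak samples were not taken at a common time, using one may need further assay runs on stored plasma; whether aliquots remain is not stated. Effects truly shared by metformin and AP would stay descriptive. Section 3.4 reports the metformin results as already published, so the change matters most for the AP report and the three-way comparison. New time-control draws are not proposed: section 2.3.7 says that eligible subjects "will then be asked to attend a method validation visit to collect additional blood and urine samples", but not that this visit is undosed and fasted, and it may already be past.

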## Abstract

This protocol aims to profile the pharmacokinetics of metformin and *Andrographis paniculata* (AP) and continue with untargeted pharmacometabolomics analysis on pre-dose and post-dose samples to characterise the metabolomics profiling associated with the human metabolic pathways. This is a single-centre, open-labelled, three periods, crossover, randomised-controlled, single-dose oral administration pharmacokinetics and metabolomics trial of metformin 1000 mg (*n* = 18), AP 1000 mg (*n* = 18), or AP 2000 mg (*n* = 18) in healthy volunteers under the fasting condition. Subjects will be screened according to a list of inclusion and exclusion criteria. Investigational products will be administered according to the scheduled timeline. Vital signs and adverse events will be monitor periodically, and standardized meals will be provided to the subjects. Fifteen blood samples will be collected over 24 h, and four urine samples will be collected within a 12 h period. Onsite safety monitoring throughout the study and seven-day phone call safety follow-up will be compiled after the last dose of administration. The plasma samples will be analysed for the pharmacokinetics parameters to estimate the drug maximum plasma concentration. Untargeted metabolomic analysis between pre-dose and maximum plasma concentration (Cmax) samples will be performed for metabolomic profiling to identify the dysregulation of human metabolic pathways that link to the pharmacodynamics effects. The metformin arm will focus on the individualised Cmax plasma concentration for metabolomics study and used as a model drug. After this, an investigation of the dose-dependent effects will be performed between pre-dose samples and median Cmax concentration samples in the AP 1000 mg and AP 2000 mg arms for metabolomics study. The study protocol utilises a crossover study design to incorporate a metabolomics-based study into pharmacokinetics trial in the drug development program. The combination analyses will complement the interpretation of pharmacological effects according to the bioavailability of the drug.

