## 2. Materials and Methods

### 2.1. Study Design

This was a single-centre, open-labelled, three periods, six sequences, crossover, single-dose oral administration, randomised-controlled trial in healthy volunteers under the fasting condition. Approximately 24 to 27 subjects were screened for a list of inclusion and exclusion criteria (Figure 1) to recruit up to 18 healthy volunteers with the estimation of 30–50% ineligibility. For AP formulation, the time to reach the maximum plasma concentration (Tmax) and the half-life (T_1/2_) were recorded at 1.63 to 2 h and 6 h, respectively [22,23]. In the package insert of metformin, the Tmax and T_1/2_ for metformin are 2 h and 6.2 h [24]. As a result, the wash-out period was determined to be seven days, which is more than five half-lives of the investigation products to ensure that the drug concentrations were below the lower limit of bioanalytical quantification in all subjects at the beginning of the next period [25]. Eligible subjects were randomised in a ratio of 1:1:1 into either metformin 1000 mg, AP capsules 1000 mg, or AP capsules 2000 mg. Figure 2 describes the SPIRIT schedule of enrolment, assessment, and intervention for the explanation to the trial subjects.

In the early-phase clinical trial, absorption, distribution, elimination, and its interaction and adverse reactions were studied in pharmacokinetics [26]. A bioavailability study measures the rate and extent of the active ingredients from the pharmaceutical dosage into the site of action, and provides information for the absorption, distribution, and elimination of a compound through a plasma concentration–time curve [27]. Generally, a crossover design is potentially affected by carry-over effects, sequence assignment, subject drops-out, and difficulties in analyses [28]. The crossover study was chosen in this single-dose oral administration proof-of-concept trial to reduce the number of subject recruitment and reduce the intrasubject variability in the metabolomics analyses. In addition, the relative short half-life of the investigational products also reduced the carry-over effects and shorten the trial period when compared to the parallel design.

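### The feature-selection t-test compares samples from the same 18 subjects, but the plan states neither pairing nor an error-rate limit for the untargeted screen

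*Protocol article*

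**What the plan says.** Section 3.3 sets out the untargeted metabolomics in order. Samples are run in positive and negative ion modes. Principal component analysis and PLS-DA are used to look at separation between time points. Then "a t-test will be used to identify the significantly differentiated compounds between the two-time point groups". The next step is: "The significant features will be processed in MS peaks to a pathway module to identify the dysregulated human metabolic pathways". The same framework is repeated for AP 1000 mg and AP 2000 mg. The resulting pathways are compared between the two AP doses and finally across all three formulations.

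The abstract identifies the samples: "Untargeted metabolomic analysis between pre-dose and maximum plasma concentration (Cmax) samples will be performed". The peak sample is individualised for metformin and median-based for the AP arms. In both cases the two samples come from the same person.

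Section 2.3.6 gives the number of pairs: "This study will recruit 18 subjects in each formulation". For the pharmacokinetic objective it says "so there is no statistical basis to determine the sample size". For metabolomics it cites a method that gives "18 subjects in each group for the probabilistic principal components and covariates analysis". No alpha, power, effect size, variance or FDR level appears in the article.

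**The concern.** For each formulation, every feature is measured twice in each of 18 subjects. The natural analysis uses 18 within-subject differences. Wording that speaks of a t-test between two groups leaves open an analysis of two independent sets of 18, which leaves the between-subject variance in the error term.

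An untargeted screen also tests very many features at once. The word significant, with no threshold behind it, leaves open selection at a per-feature 5% level.

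This t-test is the only inferential step described ahead of the pathway results. Those results are compared between AP doses for dose dependence and between metformin and AP for diabetes-related pathways. Low power or chance selections in one list could therefore pass for a dose or drug difference.

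**Working it through.** **The plan's own figure.** The 18 subjects per formulation cannot be reproduced by formula, because the article gives no alpha, power, effect size or variance. The check therefore takes n = 18 as given and asks what each reading of the t-test does with it.

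**Inputs**
- From the protocol article: n = 18 pairs (2.3.6); two ion modes and three formulations (3.3).
- Assumed, because the article does not give them: two-sided alpha 0.05 per feature; shift d = 0.5 or 0.8 SD; within-subject correlation r from 0 to 0.8; 2,000 to 5,000 unchanged features per screen, a screen being one ion mode in one formulation.

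**Step 1: power**

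Paired test: noncentral t with 17 degrees of freedom, critical value 2.110 and noncentrality d × √18 / √(2(1 − r)). At d = 0.5 and r = 0.5 this is 0.5 × 4.243 / 1 = 2.121, giving 52% power.

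Unpaired test on the same correlated pairs: two-sample t with 34 degrees of freedom and critical value 2.032, simulated with 200,000 draws.

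| d | r | Paired | Unpaired |
|---|---|---|---|
| 0.5 | 0 | 29% | 31% |
| 0.5 | 0.3 | 39% | 28% |
| 0.5 | 0.5 | 52% | 25% |
| 0.5 | 0.7 | 73% | 21% |
| 0.5 | 0.8 | 89% | 18% |
| 0.8 | 0 | 62% | 64% |
| 0.8 | 0.5 | 89% | 70% |
| 0.8 | 0.7 | 98% | 73% |

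**Step 2: real per-feature error of the unpaired test**

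The same simulation with d = 0 rejects 5.0% at r = 0, 2.1% at r = 0.3, 0.8% at r = 0.5 and 0.1% at r = 0.7. With positive correlation the unpaired test is conservative.

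**Step 3: chance selections per screen**

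Expected number = unchanged features × per-feature error.
- Paired and unadjusted: 2,000 × 0.05 = 100; 5,000 × 0.05 = 250.
- Unpaired and unadjusted at r = 0.5: 2,000 × 0.008 = 16; 5,000 × 0.008 = 40.

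As a share of what is selected, take 1,000 features of which 10% truly shift by 0.8 SD, with r = 0.5, paired and unadjusted. Chance selections are 900 × 0.05 = 45 and true ones are 100 × 0.892 = 89. So 45 / (45 + 89) = 34% of the selected features are false.

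**Step 4: pairing and Benjamini-Hochberg together**

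Simulation with 1,000 features, 10% truly shifted by 0.8 SD, FDR limit 5%, 300 runs:

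| r | Test | Power per feature | False features | Realised FDR |
|---|---|---|---|---|
| 0.5 | Paired | 47% | 2.3 | 4.6% |
| 0.7 | Paired | 84% | 3.9 | 4.4% |
| 0.5 | Unpaired | 2.6% | about 0 | about 0 |
| 0.7 | Unpaired | 1.0% | about 0 | about 0 |

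An FDR limit on an unpaired test would leave almost nothing, and pairing without an FDR limit brings in the full 5% load of chance features. The two changes belong together.

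**The case against.** The strongest reply is that the article is silent rather than wrong. A paired t-test is a t-test, and the phrase about time-point groups may only label the two occasions. The article refers its workflow to Supplementary Figure S8 and its full protocol to Supplementary Document S1, neither of which is shown, and an article may leave such detail to them. The study also calls itself a proof-of-concept exploration.

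Much of this stands. A reader might infer that the plan prescribes an unpaired, unadjusted test; the text does not say so. What remains is that section 3.3 does state a selection rule, from test to pathway step, and that rule is worse than an available alternative under either reading. This goes beyond a missing technical detail.

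A reader might also infer more than the documents support:
- **That both harms occur together.** They do not. The 100 to 250 chance features arise with a valid paired test, which loses no power. The unpaired test that loses power selects far fewer by chance (Step 3).
- **That the crossover's benefit is forfeited.** Section 2.1 justifies the crossover as a way to "reduce the intrasubject variability in the metabolomics analyses", but the pre-dose to peak contrast lies within one period and would be within-subject in a parallel trial too.
- **That PLS-DA is a source of false claims.** The article uses it only to inspect separation, and features are chosen afterwards by the t-test.
- **That the pathway step lacks a proper background list.** The article does not say what reference list the module uses, so this cannot be judged from it.

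**Conclusion.** The concern holds in a limited form. The feature-selection rule in section 3.3 is under-specified on the two choices that determine what it delivers, and the wording leaves room for a poor choice on each.

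The size is conditional. Under an unpaired reading, power falls by about half or more for a 0.5 SD shift at correlation 0.5 or above, by less for a 0.8 SD shift, and not at all at correlation 0. Under a paired, unadjusted reading, about one unchanged feature in twenty is selected. Effect sizes, correlations, feature counts and alpha are assumptions throughout, so these figures show the scale of the problem and do not predict this trial's results.

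Severity is moderate. The analysis is exploratory with no confirmatory claim at stake, but its pathway lists are the main metabolomics output and are compared across doses and drugs.

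**What to change.** State in section 3.3 that:
1. features are tested by a paired t-test on within-subject differences in log intensity, peak minus pre-dose;
2. features are selected at a stated Benjamini-Hochberg FDR, for example 5%, applied within each ion mode and formulation.

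Apply this to the two AP analyses, which section 3.4 still describes as to be reported. That section says the metformin analysis has been published, so for metformin run it as a re-analysis or sensitivity analysis, to put the final comparison of the three formulations on one rule. If the supplementary files already fix both points, one sentence in section 3.3 is enough.

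No new subjects or samples are needed. The cost is a change of wording and settings, a little re-analysis for metformin, and a shorter feature list than unadjusted paired testing would give. In the Step 4 setting at correlation 0.5, per-feature power falls from 89% unadjusted to 47% at 5% FDR, while the false share of selections falls from about 34% to under 5%.
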